## Trial intervention

### OTIS trial usual care group

Participants will receive usual care from their general practitioner (GP) and other healthcare professionals, which may include referrals to a falls clinic. Participants will receive a falls prevention advice leaflet produced by Age UK (‘Staying steady’ published in June 2015) with their baseline questionnaire in the post. A group-specific newsletter will be sent to participants at 3 months postrandomisation and 2 weeks before their 12-month follow-up questionnaire is due, informing them about study progress. All participants will receive a pen and £5 with their 12-month follow-up questionnaire in recognition of their participation and to offset any incidental expenses associated with completing the questionnaires.

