### OTIS trial intervention group

In addition to the usual care and falls prevention leaflet described above, participants allocated to the intervention arm will be offered a home environmental assessment to identify personal fall-related hazards and behaviours. The assessment will be undertaken by a Health and Care Professions Council registered OT and will take approximately 2 hours to conduct. If the assessment is too demanding for the participant, the appointment may be split over two visits. OTs will attend a 1-day face-to-face training session on how to conduct the assessment. This will be provided by either the researcher who carried out the pilot trial (AP) or two of the OT researchers ([name] and AD) who will be trained by AP to deliver the training in a standardised way.

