#### Delivery of treatment

An observational study will be undertaken over the course of the trial to assess how the treatment was delivered. An OT who delivered the intervention training will shadow OTs while they visit participants. A checklist will be used to record which elements of the intervention are delivered. We will purposively sample OTs for shadowing to ensure we select a sample of OTs who attended different training sessions and who delivered either several or few assessments. Approximately 10 OTs will be observed. While this is a small number of observations involving approximately half of the OTs delivering the intervention, if a greater number were undertaken, then the observation itself would become part of the intervention. Consent for an additional, observing OT to attend the home visit will be obtained from the participant. Participants will be able to decline the second OT attending the visit at any point during the process and will still be able to receive a home visit. Elements of fidelity will also be included in the qualitative interviews. A similar sampling strategy to that detailed above will be used.

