### Statistical analysis of the OTIS primary outcome

The number of falls per person will be analysed using Poisson regression (or negative binomial regression, as appropriate) adjusting for gender, age, history of falling and the allocation ratio used to randomise the participant as fixed effects. The model will include an exposure variable for the number of months that the participant returned a monthly falls calendar. A sensitivity analysis will be conducted to account for potential clustering effects by the OT by assigning every randomised participant an OT irrespective of group allocation. For intervention participants, this will be the OT delivering their intervention, whereas for control participants, a counterfactual therapist, that is, one that they could have seen had they been randomised to the intervention group, will be randomly assigned to them. Therapist will then be included as a random effect in the primary analysis model. Additionally, a Complier Average Causal Effect analysis to assess the impact of compliance on treatment estimates will be undertaken for the primary analysis.

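### The sensitivity analysis for therapist clustering uses one random effect shared by both arms, so it cannot register clustering that arises only where the OTs deliver the intervention

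*Protocol article*

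**What the plan says.** All of this is in the protocol article.

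- **Primary model** (in the Statistical analysis of the OTIS primary outcome section): "The number of falls per person will be analysed using Poisson regression (or negative binomial regression, as appropriate", with fixed-effect covariates and no therapist or site term.
- **Purpose of the check** (same section): "A sensitivity analysis will be conducted to account for potential clustering effects by the OT by assigning every randomised participant an OT irrespective of group".
- **Therapist label, intervention arm:** "For intervention participants, this will be the OT delivering their intervention".
- **Therapist label, control arm:** a counterfactual therapist, "one that they could have seen had they been randomised to the intervention group, will be randomly assigned to them".
- **Model:** "Therapist will then be included as a random effect in the primary analysis model". No treatment-by-therapist term and no arm-specific therapist variance is stated.
- **Who meets an OT:** under OTIS trial intervention group, "participants allocated to the intervention arm will be offered a home environmental assessment to identify personal fall-related hazards and behaviours". The section on the control arm reads: "Participants will receive usual care from their general practitioner (GP) and other healthcare professionals, which may include referrals to a falls clinic"; no trial OT visit is part of that arm.
- **Number of OTs:** under Delivery of treatment, about 10 OTs will be observed, described as "approximately half of the OTs delivering the intervention". That implies about 20.

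**The concern.** If some OTs deliver the assessment more effectively than others, outcomes of participants seen by the same OT are correlated, and the treatment estimate varies more than an independent-observations model allows. In this trial that can happen only in the intervention arm.

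Labelling controls with OTs crosses OT with arm. A single intercept per OT then says that OT *j* shifts the fall rate of treated participants and of labelled controls by the same amount. That common shift drops out when the arms are compared within an OT, so the between-OT variance never reaches the SE of the treatment effect. Controls labelled with OTs they never met show no therapist effect, and so also pull the estimated OT variance towards zero.

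The primary model has no therapist term, so this is the only stated check on OT clustering. If it returns nearly the same SE whatever the OT variance in the intervention arm, agreement with the primary analysis is no evidence that therapist clustering is unimportant.

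**Working it through.** **The plan's own figures.** The protocol gives none for therapist clustering. Its sample-size figures reproduce: 60% v 50%, two-sided 5%, 90% power and 2:1 give 776 + 388 = 1164, and 1164/0.9 = 1294 against the stated 1299. After 10% loss, power is 90.1% at 866/433 and 84.8% at 974/325.

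**Inputs.** From the protocol: 866 control, 433 intervention, and about 20 OTs (10 is about half). Assumed: intervention-arm ICC of 0.01, 0.02 or 0.05, and 15 to 25 OTs as a range.

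**Step 1: analytic check.** Take a linear model, residual variance 1, *T* OTs with equal caseloads and the same allocation ratio within each OT.

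- Variance reported with a shared intercept (it cancels): 1/866 + 1/433 = 0.003464.
- True variance with an OT effect in the intervention arm only: 0.003464 + s²/*T*, where s² = ICC/(1 − ICC).
- SE ratio *r* = √(true/reported). Type I error = 2[1 − Φ(1.96/*r*)].

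| ICC (20 OTs) | s²/20 | *r* | Type I error |
|---|---|---|---|
| 0.01 | 0.000505 | 1.07 | 6.7% |
| 0.02 | 0.001020 | 1.14 | 8.5% |
| 0.05 | 0.002632 | 1.33 | 14.0% |

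Over 15 to 25 OTs and the same ICCs, type I error runs from 6.4% to 16.7%. With 10% attrition in each arm (779.4 v 389.7) the ratios at 20 OTs are 1.06, 1.12 and 1.30, so the picture is the same.

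**Step 2: does the cancellation survive in a count model?** Exact cancellation needs a linear model and a constant allocation ratio. A negative binomial simulation therefore used 866 v 433, 20 OTs with unequal caseloads, random OT labels for controls, no true marginal effect, and 1000 trials per scenario. Mean 1.5 falls and dispersion 1 are assumptions; they give 1 − 1/(1 + 1.5) = 60% fallers. OT variation was in the intervention arm only.

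| OT SD (log rate) | SE, no OT term | SE, planned model | Empirical SD, planned model | Type I, no OT term | Type I, planned model | Median OT SD, planned model |
|---|---|---|---|---|---|---|
| 0 | 0.0760 | 0.0760 | 0.0722 | 3.6% | 3.5% | 0.01 |
| 0.2 | 0.0764 | 0.0765 | 0.0940 | 10.7% | 10.7% | 0.04 |
| 0.3 | 0.0769 | 0.0771 | 0.1126 | 17.8% | 17.0% | 0.09 |
| 0.4 | 0.0777 | 0.0781 | 0.1340 | 26.7% | 25.0% | 0.12 |

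The planned term raises the SE by at most 0.5% (0.0781/0.0777), and that SE is 81%, 69% and 58% of the true sampling SD at OT SD 0.2, 0.3 and 0.4. On the log scale the per-person variance is roughly 1/1.5 + 1 = 1.67, so these SDs correspond to ICCs of about 0.04/1.71 = 0.02, 0.09/1.76 = 0.05 and 0.16/1.83 = 0.09. The third lies beyond the range in Step 1.

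**Step 3: what the planned term does handle.** With OT-level variation of SD 0.3 common to both arms, the same simulation gave the planned model SE 0.0775 against empirical SD 0.0764, and 5.3% type I error.

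**Step 4: which replacement works?** Gaussian simulation, 20 OTs, 400 v 800, ICC 0.05.

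| Source of variation | Model | SE | True SD | Rejection |
|---|---|---|---|---|
| Intervention arm only | No OT term | 0.0612 | 0.080 | – |
| Intervention arm only | Shared intercept (planned) | 0.0615 | 0.080 | 13% |
| Intervention arm only | Shared intercept + random treatment coefficient | 0.078 | 0.080 | – |
| Area, shared by both arms | OT effect in intervention arm only | 0.078 | 0.061 | 2% |
| Area, shared by both arms | Shared intercept + random treatment coefficient | 0.064 | 0.061 | 4.4% |

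A dash means that no rate is quoted for that row. Only the model with both terms gives an SE close to the true SD in both settings.

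**The case against.** **The planned term is not empty.** Participants are randomised in blocks within site, and a control's counterfactual OT must be one they could have seen. The label therefore carries locality, and the primary model has no site term. Step 3 shows the shared effect working when variation is common to both arms. This stands. A reader might infer that the analysis corrects for no clustering at all, but that goes too far: it fails for clustering by delivery, which is what its stated purpose names.

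**An effect in the intervention arm alone would bring its own error.** This also stands. With shared area variation it reads area differences as therapist variance and over-widens the interval (Step 4), so the shared intercept should be supplemented, not swapped out.

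**It is only a sensitivity analysis, and the ICC is unknown.** Both true. The protocol uses a standard 57-item checklist and standardised training, which should limit differences between OTs, although recommendations are tailored to the participant. The ICC may be at the low end, where the effect is modest.

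**A condensed article leaves model detail to the analysis plan.** Often so, but here the article states the labelling of controls, the purpose and a single therapist random effect. A shared intercept is the natural reading. If the full plan already lets the therapist effect differ by arm, the point is met.

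**Conclusion.** The concern holds in a limited form. As written, the check on OT clustering leaves the treatment SE essentially where it is with no clustering term, because delivery clustering sits in one arm and the random effect is shared by both. At about 20 OTs, the planned SE is too small by a factor of about 1.07 to 1.33 for an assumed ICC of 0.01 to 0.05, with type I error of about 7% to 14%. These figures rest on the assumed ICC, on equal caseloads and on the OT count implied by the fidelity section. The harm vanishes if therapist variance is zero.

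Two stronger readings are not supported.

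- A reader might infer that the flaw biases the primary estimate. It does not: that estimate comes from a separate model, and what is lost is the value of the check on it.
- A reader might infer that the stated power is wrong. The 90% and 85% figures reproduce under their stated conditions. The sample-size section makes no claim about clustering, and power is a separate question from how this model is specified.

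**What to change.** Within this sensitivity analysis only:

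1. Add a random treatment coefficient by OT, that is, a therapist effect acting in the intervention arm only.
2. Keep a shared intercept for site or area, or for OT, so that local variation common to both arms is not read as therapist variance. With a site intercept, controls no longer need a counterfactual OT and the result no longer depends on a random draw. With an OT intercept, the assignment stays.
3. Use a small-sample correction suited to about 20 clusters. In the count simulation, even a model with the OT effect in the intervention arm rejected 6.3% to 7.1% without one.
4. Report the intervention-arm OT variance alongside the rate ratio and its confidence interval.

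The cost is one more variance component to estimate and a possibly wider interval in this sensitivity analysis. No new outcome data are needed, and the primary analysis and sample size are unchanged.

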### Secondary analysis

The following outcomes will be analysed by logistic regression adjusted for the same covariates as the primary analysis model: the proportion of participants who fall at least once over the 12-month period from the date of randomisation; the proportion of multiple fallers (two or more falls in the 12 months from randomisation); the proportion of participants having at least one fracture over the 12-month follow-up; the proportion of patients obtaining multiple fractures (from different events, if this occurs a sufficient number of times); and the proportion of participants who report that they are worried about falling at 12-month postrandomisation.

Fear of falling will also be analysed in its continuous form using a covariance pattern model incorporating all postrandomisation time points in the analysis and adjusting for baseline score, gender, age, history of falling, allocation ratio, treatment group, time and a treatment group-by-time interaction. The correlation of observations within patients over time will be modelled.

The time to the first fall will be derived as the number of days from randomisation until the patient reports having a fall as detailed in the participant’s falls calendars. Time between any subsequent falls will also be calculated. Participants who have not had a fall will be treated as censored at their date of trial exit, or date of last available assessment or 365 days/trial cessation, as appropriate. The proportion of patients yet to experience a fall will be summarised by a Kaplan-Meier survival curve for each group. Time to fall will be analysed using the Andersen and Gill method for analysing time to event data when the event can be repeated. The analysis treats each time to event or censoring as a separate observation. The data will be analysed by Cox proportional hazards regression using robust SEs to account for dependent observations by participant and adjusting for the same covariates as in the primary analysis model.

Adherence to the WeHSA and results of the TUG will also be summarised descriptively.

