### OTIS trial secondary outcomes

All secondary outcomes will be self-reported by the participant and collected via questionnaires at baseline, 4, 8 and 12 months or by monthly falls calendars. They include: proportion of participants reporting at least one fall in the 12 months from randomisation; proportion of participants reporting multiple (two or more) falls in the 12 months from randomisation; time to first fall from date of randomisation; health-related quality of life as measured by the EQ-5D-5L^23^; fracture rate; fear of falling as measured by the question ‘During the past 4 weeks have you worried about having a fall?’; and health service utilisation.

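### The 12-month logistic model for worry about falling leaves out the baseline answer to the same question, which is collected and is adjusted for in the continuous analysis

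*Protocol article*

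**What the plan says.** Under Secondary analysis, the protocol article sets one model for five binary outcomes: "The following outcomes will be analysed by logistic regression adjusted for the same covariates as the primary analysis model". The last outcome in that list is "the proportion of participants who report that they are worried about falling at 12-month postrandomisation". The covariates follow by cross-reference to Statistical analysis of the OTIS primary outcome, which specifies a model "adjusting for gender, age, history of falling and the allocation ratio used to randomise the participant as fixed effects".

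The next paragraph of Secondary analysis returns to the same item: "Fear of falling will also be analysed in its continuous form using a covariance pattern model". That model uses all post-randomisation time points and is fitted "adjusting for baseline score, gender, age, history of falling, allocation ratio, treatment group, time and a treatment group-by-time interaction".

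OTIS trial secondary outcomes defines fear of falling by a single question about worry over the past four weeks. It says that secondary outcomes are "collected via questionnaires at baseline, 4, 8 and 12 months", or by the monthly calendars. Under Advertising for participants, the article requires a valid baseline questionnaire before randomisation.

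**The concern.** Worry is the only outcome in the logistic list that is a state measured at baseline and then again on the same question. The other four count falls or fractures after randomisation, and for those the primary-model covariates are a natural choice. Placing worry in the same list gives it a covariate set without its own baseline value, while the continuous analysis of the same item includes that value. The article gives no reason for the difference. The covariate set is stated explicitly, so this is not a detail left open for the analysis plan.

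Two things are at stake for the binary estimate: power, if worry at baseline predicts worry at 12 months, and protection against a chance difference between arms in baseline worry.

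**Working it through.** **1. Numbers analysed.** The article randomises 866 to usual care and 433 to intervention and allows 10% attrition: 866 × 0.9 = 779.4 and 433 × 0.9 = 389.7, so about 779 v 390.

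**2. The plan's own figure.** No power is stated for worry. The design figure is for at least one fall, 60% v 50%, two-sided 5%, 90% power. With k = 0.5 and no continuity correction,

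n₁ = [1.960·√(p̄q̄(1 + 1/k)) + 1.2816·√(p₁q₁ + p₂q₂/k)]² / (p₁ − p₂)²

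Here p̄ = (0.6 + 0.5 × 0.5)/1.5 = 0.5667. This gives n₁ = 776 and n₂ = 388, a total of 1164. Dividing by 0.9 gives 1294, against 1299 stated. Power after attrition is 90.1% at 2:1 and 84.8% at 3:1 (stated: 90% and 85%). The design figures reproduce and are unaffected by this point.

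**3. Planned covariates side by side.**

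| | Binary, 12 months | Continuous, all time points |
|---|---|---|
| Gender, age, history of falling, allocation ratio | yes | yes |
| Baseline worry | no | yes |

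**4. Power without baseline (assumed rates).** Take 12-month worry as 50% v 42%. The standard error is √(0.25/779 + 0.2436/390) = 0.03075, so z = 0.08/0.03075 = 2.60. Power is about Φ(2.60 − 1.96) = Φ(0.64), or 74%.

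**5. Power with baseline, by assumed odds ratio linking baseline to 12-month worry.** Simulation: 2000 trials per setting, logistic model with treatment alone, then with binary baseline worry added. Entries are power in % without → with baseline.

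| Baseline worry | OR 1 | OR 3 | OR 6 | OR 10 | OR 20 |
|---|---|---|---|---|---|
| 40% | 76 → 76 | 74 → 78 | 75 → 80 | 74 → 85 | 74 → 90 |
| 60% | 74 → 74 | 73 → 75 | 73 → 81 | 75 → 85 | 76 → 89 |
| 80% | 75 → 74 | 73 → 73 | 74 → 77 | 73 → 79 | 75 → 81 |

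The gain is small at OR 3, about 3–8 points at 6, 5–11 at 10 and 6–16 at 20. Type I error is about 4% to 6% with or without the covariate.

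**6. The same question by assumed latent correlation.** An underlying normal worry score is shifted by 0.2 SD in the intervention arm, with baseline worry at 50% or 70%. A control rate of 50% then becomes Φ(−0.2) = 42%, which matches step 4. Power without baseline is about 73%.

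| Correlation | Gain, baseline worried or not | Gain, graded baseline |
|---|---|---|
| 0.3 | about 1–2 points | about 1–2 points |
| 0.5 | about 3–5 | about 5–7 |
| 0.6 | about 5–7 | about 9–11 |
| 0.7 | about 7–11 | about 13–14 |

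**7. Effect measure.** In step 5 the treatment odds ratio without baseline is 0.42/0.58 ÷ 1 = 0.724. Conditional on baseline, the same marginal rates correspond to 0.655 (baseline worry 60%, OR 10) or 0.592 (40%, OR 20). The adjusted odds ratio lies further from 1 because it answers a conditional question, not because the effect is larger.

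**The case against.** The best defence is that the plan already reports a baseline-adjusted analysis of this item. The continuous model uses baseline score and every follow-up time point, and baseline data are to be summarised by arm, so an imbalance would be visible. The outcome is secondary, the trial is not powered on it, and randomisation keeps the test valid. All of that stands, and it makes the point a small one. It does not supply the missing adjustment for the binary estimate, which will be reported in its own right.

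The size is also open to challenge. The simulations compare against a model containing treatment only. The planned model includes history of falling, which may already carry part of the information, so the real gain could be smaller. With a weak baseline-to-12-month link there is almost none.

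A reader might infer more than the article supports:

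- That the binary and continuous results could disagree only because one ignores baseline. They also differ in scale, time points and model, and could still disagree after the fix.
- That baseline worry is itself an entry criterion. Eligibility uses fear of falling on the screening questionnaire, as an alternative to a past fall. The article does not say that this item is the four-week worry question.
- That baseline worry is the strongest predictor of 12-month worry. That is a reasonable expectation, but no figure in the article shows it.

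**Conclusion.** The point holds as one of efficiency and consistency. The 12-month logistic model for worry omits a baseline value that the trial collects and that the plan uses for the same item elsewhere. It is not an error of validity: false-positive control is unaffected, and neither the primary analysis nor the sample size changes.

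The gain forgone depends on how strongly baseline worry tracks 12-month worry, which the article does not report. Across assumed latent correlations of 0.3 to 0.7, with 779 v 390 analysed and about 73% power without baseline, it runs from about 1–2 points to about 7–11 points with binary coding or 13–14 with graded coding. The upper figures need both a strong correlation and a graded baseline score.

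**What to change.** Add the baseline response to the four-week worry question as a covariate in the 12-month logistic model, alongside gender, age, history of falling and allocation ratio. Preferably enter it as the graded score used in the continuous model, since that recovers more than a worried-or-not indicator. State the coding before analysis. Note with the result that the odds ratio is conditional on baseline worry, so it is not directly comparable with one that is not so adjusted.

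The cost is one covariate and a line or two in the analysis plan. No new data are needed, because the item is on the baseline questionnaire. Participants who left the item blank at baseline will need a stated handling rule. The other four outcomes in the logistic list can keep the primary-model covariates.

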**Methods and analysis:**

A two-arm, modified cohort randomised controlled trial, conducted within England, with 1299 community-dwelling participants aged 65 years and above, who are at an increased risk of falls. Participants will be randomised 2:1 to receive either usual care or home assessment and modification. The primary outcome is rate of falls (falls/person/time) over 12 months assessed by monthly patient self-report falls calendars. Secondary self-reported outcome measures include: the proportion of single and multiple fallers, time to first fall over a 12-month period, quality of life (EuroQoL EQ-5D-5L) and health service utilisation at 4, 8 and 12 months. A nested qualitative study will examine the feasibility of providing the intervention and explore barriers, facilitators, workload implications and readiness to employ these interventions into routine practice. An economic evaluation will assess value for money in terms of cost per fall averted.

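### Time to first fall is a listed secondary outcome, but the only between-arm time-to-event model planned is an Andersen-Gill model of all falls, which targets a different quantity

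*Protocol article*

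**What the plan says.** The outcome is named twice, and both times as the first fall. The abstract lists "time to first fall over a 12-month period", and the section on secondary outcomes lists "time to first fall from date of randomisation".

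The Secondary analysis section then proceeds as follows:

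- It derives the named variable: "The time to the first fall will be derived as the number of days from randomisation until the patient reports having a fall".
- It adds later falls to the dataset: "Time between any subsequent falls will also be calculated".
- It describes first falls by arm: "The proportion of patients yet to experience a fall will be summarised by a Kaplan-Meier survival curve for each group".
- It names the model: "Time to fall will be analysed using the Andersen and Gill method for analysing time to event data when the event can be repeated".
- It defines the unit of analysis: "The analysis treats each time to event or censoring as a separate observation".
- It specifies the fit as "Cox proportional hazards regression using robust SEs to account for dependent observations by participant", with the primary model's covariates.

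Separately, the same section plans an adjusted logistic regression for having at least one fall within 12 months. The primary outcome is the number of falls per participant over 12 months. It is analysed by Poisson or negative binomial regression, with months of returned calendars as exposure.

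**The concern.** The derivation and the plot concern the first fall, but the model counts every fall as an event. The closing Cox sentence cannot be read as a second model restricted to first falls. Its robust standard errors are there for dependence within a participant, which arises only when a participant contributes more than one record. No log-rank test or first-event Cox model is given.

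As written, the trial would therefore have no between-arm estimate or test of the timing of the first fall, although that is a listed outcome. If the Andersen-Gill ratio were reported under that label, readers would take a ratio of overall fall rates for a first-fall hazard ratio. The two can differ in size, and in some patterns of effect one is present without the other.

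**Working it through.** **1. The plan's own figure.** The article gives no number for this analysis, so its sample size was checked to fix the design inputs: 60% v 50% with at least one fall, 2:1 allocation, two-sided 5%, 90% power, 10% attrition.

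- The weighted mean proportion is (0.5 + 2 × 0.6)/3 = 0.567.
- n(intervention) = [1.960 × √(1.5 × 0.567 × 0.433) + 1.282 × √(0.25 + 0.24/2)]² / 0.10² = 388.
- With 776 controls the total is 1164, and 1164/0.9 gives 1294, against 1299 stated.
- Power is 90.1% at 2:1 and 84.8% at 3:1, against 90% and 85% stated.

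The sample size reproduces and is not at issue.

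**2. What Andersen-Gill estimates.** Take complete 12-month follow-up and no covariates. All n1 intervention and n0 control participants are then at risk throughout. With E1 and E0 falls, the score equation is

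E1 = (E1 + E0) × n1·e^β / (n1·e^β + n0), so e^β = (E1/n1)/(E0/n0).

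This is the ratio of mean fall counts, which an unadjusted Poisson model with equal exposure also gives. With incomplete calendars, covariates or a negative binomial likelihood the two estimates will differ somewhat, but the target is still the overall rate ratio.

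**3. What a first-fall comparison estimates.** Assume falls follow a Poisson process with gamma heterogeneity of dispersion θ (not given in the article) and control mean μ. Then P(no fall) = (1 + θμ)^(−1/θ). Setting this to 0.40 in controls and applying a rate ratio of 0.75 to every fall gives:

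| θ | Control mean | Intervention mean | P(no fall), intervention | 12-month cumulative first-fall hazard ratio |
|---|---|---|---|---|
| 0 | 0.916 | 0.687 | 0.503 | 0.75 |
| 1 | 1.50 | 1.125 | 1/2.125 = 0.471 | ln(0.471)/ln(0.4) = 0.82 |
| 1.5 | 1.97 | 1.48 | 3.215^(−2/3) = 0.459 | ln(0.459)/ln(0.4) = 0.85 |

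Fitted Cox hazard ratios in simulation at θ = 1 and 1.5 were 0.81 and 0.84. Together these give the range of about 0.81 to 0.85.

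**4. The same comparison from the design proportions.** For 60% v 50%, the cumulative first-fall hazard ratio is ln(0.5)/ln(0.4) = 0.76. The mean-count ratio for those same proportions is 1.00/1.50 = 0.67 at θ = 1 and 1.22/1.97 = 0.62 at θ = 1.5.

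**5. Simulation of different effect patterns.** There were 390 v 779 evaluable participants (433 and 866 less 10%), complete follow-up, 60% of controls falling and 150 runs per scenario, unadjusted. Frailty was none, or gamma with shape 1.5 or 0.8 (dispersion 0.67 or 1.25).

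| Effect | Andersen-Gill ratio | Significant | First-fall hazard ratio | Significant |
|---|---|---|---|---|
| 0.75 on every fall | about 0.75 | 93–98% | 0.75–0.83 | 65–93% |
| 0.70 on second and later falls only | 0.80–0.90 | 41–78% | 0.99–1.00 | 5–7% |
| 0.75 on first fall only | 0.82–0.89 | 27–74% | 0.75–0.82 | 69–90% |

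Monte Carlo error on the percentages is up to about 8 points. The second row shows most clearly that Andersen-Gill does not test the first fall: it is often significant when the first-fall hazard is unchanged.

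**The case against.** The mismatch itself is hard to dispute, but several stronger readings are tempting and the article does not support them.

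- **First fall gets no valid analysis.** A reader might infer this. The Kaplan-Meier curves validly estimate the first-fall distribution in each arm, and the logistic model tests whether any fall occurred by 12 months. What is missing is a between-arm estimate or test of timing.
- **The primary analysis is simply run twice and would pass for independent confirmation.** The target is essentially shared, but the models are not identical. One uses calendar months as exposure and may be negative binomial. The other uses event times, censoring and robust standard errors. Nothing in the article says the results would be presented as confirming each other.
- **Fallers leave the risk set, or the model runs on gap time.** Explicit censoring dates are given only for participants who never fell. However, the wording "The analysis treats each time to event or censoring as a separate observation" can cover a faller's last censored interval. The sentence "Time between any subsequent falls will also be calculated" describes a derived variable and does not set the model's time scale. The scale is not spelled out, but it is not shown to be wrong.
- **The planned model is biased by a known amount.** It estimates a different quantity, and the model sentence speaks of time to fall, not of the first fall. The dispersion values are assumed. Adjustment for age, gender, history of falling and allocation ratio would absorb some heterogeneity, so the gap may be smaller than the unadjusted figures.

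The analysis plan is not shown and may already contain a first-fall Cox model. That does not remove the point: the article does state a model in its paragraph on this outcome, and that model does not match the outcome's name.

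**Conclusion.** The concern holds in a limited form. A listed secondary outcome, time to first fall, has no matching between-arm time-to-event analysis. The only such model concerns all falls and targets essentially the primary model's rate ratio.

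The size depends on assumptions. With an equal effect on every fall and no heterogeneity, the two ratios coincide (0.75 and 0.75). With dispersion of 1 to 1.5, a rate ratio of 0.75 corresponds to a first-fall hazard ratio of about 0.81 to 0.85. If the effect differs between first and later falls, the ratios can part even without heterogeneity. The article itself allows for overdispersion through its negative binomial option, so some gap is plausible, but its size cannot be fixed from the document.

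The primary outcome, its analysis and the sample size are untouched. The change should be made, but the trial's main conclusion does not depend on it.

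**What to change.** 1. Analyse time to first fall with a Cox model in which follow-up ends at the first fall. Use the primary model's covariates and the censoring rule already in the Secondary analysis section (trial exit, last available assessment or 365 days). Report this hazard ratio with the Kaplan-Meier curves.
2. Keep Andersen-Gill, labelled as a supporting analysis of recurrent falls. State that it uses time from randomisation and that fallers remain at risk until the end of follow-up.

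The cost is a few lines in the analysis plan and one extra model on a variable that is already to be derived. Data collection and sample size do not change. If the analysis plan already contains the first-fall model, only the labelling and the time-scale statement remain to be checked.
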